### Data collection, management, and analysis

#### Data collection methods

Table 1 shows the details of data collection throughout the study period.

#### Data management

An electronic CRF will be made available to ensure data accuracy, completeness, and reliability. The research staff will preserve documented data from all sources on the CRF.

#### Statistical methods

Results will be compared using the Mann–Whitney *U* test or the Kruskal–Wallis test for categorical unpaired data. The Wilcoxon rank-sum test or the Friedman test will be used to analyze paired data. The Fisher’s exact test will be used to compare dichotomous variables. The Pearson chi-square test will be used to analyze nominal variables. The McNemar test will be used to analyze paired categorical data. The means will be compared using the two-sample test and analysis of variance or linear regression, as appropriate. However, for all aforementioned inferential analysis methods, the center effect will not be considered when comparing one treatment with another. Therefore, analysis of variance incorporating a center effect and the Cochran–Mantel–Haenszel test stratified by the center effect will be applied to replace the two-sample *t* test and the Fisher’s exact test. For efficacy analyses and part of the safety analyses (including laboratory data and vital signs data), and considering the effect of baseline data on the end points, analysis of covariance will be applied when comparing one treatment mean with another, with their respective baseline as covariates. Baseline data are defined as the data obtained before the first administration of treatment before surgery. End points are defined as the net change of post-treatment data from baseline data. Statistical analyses will be conducted using SPSS 20.0 (SPSS, Chicago, IL, USA). *P* values less than 0.05 will be considered statistically significant.

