### Sample size estimation

Using a per-protocol two-sided α of 0.025, a 2:1 randomization between regorafenib plus FOLFIRI dose escalation and regorafenib, and a median PFS of 3.2 months in the regorafenib group [9], the study would have 90% power to detect assumed median PFS of 7.0 months with regorafenib plus FOLFIRI [3]. The assumption of overall probability of events is 0.77 (10 progressions at the end of the study out of 13 in total) [9]. The calculated sample size is 121 patients. Considering a 20% drop-rate, a total of 153 patients should be enrolled into the study, with 102 assigned to the study group (FOLFIRI plus regorafenib group) and 51 to the control group (regorafenib monotherapy group).

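### The plan names the Wilcoxon rank-sum test, an independent-samples test, for paired data; the signed-rank test is what a two-time-point paired comparison needs (minor)

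*Protocol article*

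**What the plan says.** The Statistical methods section of the protocol article lists tests by type of data.

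- Unpaired data: "Results will be compared using the Mann–Whitney *U* test or the Kruskal–Wallis test for categorical unpaired data".
- Paired data: "The Wilcoxon rank-sum test or the Friedman test will be used to analyze paired data".
- Paired categories: McNemar, whose "test will be used to analyze paired categorical data".
- Efficacy and part of the safety data, expressly including laboratory values and vital signs: "analysis of covariance will be applied when comparing one treatment mean with another, with their respective baseline as covariates".
- Outcome scale: "End points are defined as the net change of post-treatment data from baseline data".
- Level: P "values less than 0.05 will be considered statistically significant".

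The section does not say which variables will be tested as paired data, and it gives no within-patient correlation. Table 1 schedules performance status, urinalysis, hematology and clinical chemistry at enrollment and again every 2 weeks, so paired measurements will exist.

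**The concern.** Mann–Whitney U and Wilcoxon rank-sum are one procedure, so the section assigns the same two-independent-sample test to unpaired data and to paired data. Its null distribution treats all 2n observations as freely exchangeable between two unrelated groups. The paired question is whether values shift within patients, and its null flips the sign of each patient's own difference. That is the signed-rank test.

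This is a method stated wrongly, not a detail left to a statistical analysis plan. An analyst who follows the text runs the wrong test on a two-time-point within-patient comparison. An analyst who runs the right one departs from the published plan. What is at stake is the calibration and power of those within-arm comparisons.

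**Working it through.** **The plan's own figure.** The disputed sentence carries no number. The article's one computed design figure is the sample size, and it does not involve this test. Sample size estimation gives medians of 3.2 and 7.0 months, 90% power, an event probability of 0.77, and: "Using a per-protocol two-sided α of 0.025, a 2:1 randomization between regorafenib plus FOLFIRI dose escalation and regorafenib". The hazard ratio is 3.2/7.0 = 0.457. Schoenfeld events = (2.2414 + 1.2816)² / [(2/3)(1/3)(ln 0.457)²] = 12.41/0.1362 = 91.2, so 92. Then 92/0.77 = 119.5, so 120 against the stated 121. With 20% dropout, 121/0.8 = 151.25, so 152, and 153 is the next multiple of 3. The design figure is reproduced closely, and no paired test enters it.

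**Inputs for the check.** Pairs per arm: 51 and 102, from Trial design, taking every enrolled patient to supply a pair. Level: 0.05 from Statistical methods; two-sided is assumed because the section does not say. Within-patient correlation ρ: not in the article, so a range is shown. Values are assumed bivariate normal.

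**Large-sample size.** Under the null, the rank-sum statistic is scaled as if the two sets of ranks were independent. With pairs, its true standard deviation is smaller by the factor √(1 − ρs), where ρs is the Spearman correlation within pairs. For bivariate normal data ρs = (6/π)·arcsin(ρ/2). So

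true size = 2·[1 − Φ(1.96/√(1 − ρs))].

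- ρ = 0.1: ρs = 0.096; 1.96/0.951 = 2.061; size 0.039.
- ρ = 0.3: ρs = 0.288; 1.96/0.844 = 2.322; size 0.020.
- ρ = 0.5: ρs = 0.483; 1.96/0.719 = 2.725; size 0.006.

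The number of pairs does not appear in the formula.

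**Simulation.** 10,000 runs per setting, normal approximation for both tests. Power is at a shift of 2.8016·√(2(1 − ρ)/n)·1.023 standard deviations (SD), chosen so that the signed-rank test has roughly 79% power. At ρ = 0.5 that is 0.40 SD with 51 pairs and 0.28 SD with 102. Paired entries are for 51 / 102 pairs.

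| ρ | size by formula | rank-sum size | signed-rank size | rank-sum power | signed-rank power |
|---|---|---|---|---|---|
| −0.3 | 0.084 | 0.087 / 0.081 | 0.051 / 0.048 | 85% / 86% | 79% / 79% |
| 0 | 0.050 | 0.050 / 0.048 | 0.051 / 0.049 | 79% / 80% | 79% / 79% |
| 0.1 | 0.039 | 0.042 / 0.043 | 0.051 / 0.052 | 76% / 76% | 78% / 79% |
| 0.2 | 0.029 | 0.028 / 0.028 | 0.046 / 0.048 | 72% / 72% | 79% / 80% |
| 0.3 | 0.020 | 0.022 / 0.019 | 0.047 / 0.049 | 66% / 66% | 78% / 79% |
| 0.5 | 0.006 | 0.007 / 0.007 | 0.047 / 0.049 | 51% / 51% | 79% / 79% |
| 0.7 | 0.0005 | 0.001 / 0.001 | 0.051 / 0.051 | 23% / 22% | 78% / 79% |

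Larger shifts are still mostly found. For 0.5 SD at ρ = 0.5, rank-sum against signed-rank power is 74% against 93% with 51 pairs, and 98% against 99.8% with 102.

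**The case against.** The strongest reply is that this is a slip of naming. The section gives a two-group and a several-group test for unpaired data, then a Wilcoxon test and Friedman for paired data; the parallel suggests that the signed-rank test was meant. That is plausible and limits the severity, but the text still says otherwise and needs correcting.

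The second reply is that other rules cover the ground. This stands in part. Friedman, in the same sentence, is valid for related samples, including the measurements taken every 2 weeks. With two time points it reduces to a sign test, which is valid but less powerful than signed-rank. It is joined by an *or* with no rule for choosing, so the wrong option remains open. McNemar is confined to categories, and analysis of covariance compares arms, so neither repairs the within-arm case. The definition of end points as change from baseline is not evidence of the error: a change score already uses the pairing, and comparing change scores between arms with a rank-sum test is legitimate.

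A reader might go further and infer that real toxicity shifts will be missed and that the error therefore runs in an unsafe direction. The article does not support this. No toxicity variable is tied to the sentence. Adverse events are graded each cycle with no paired test specified, and between-arm laboratory and vital-sign comparisons use baseline-adjusted analysis of covariance. Safety stopping rules and Data monitoring do not refer to a within-arm P value.

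**Conclusion.** Wrong as written, and minor. The misassignment is certain from the text. Its effect is conditional on a positive within-patient correlation, which the article does not give. It would be too strong to say without qualification that the test runs far below its nominal level: that is so at correlations of about 0.5 or more, but the loss is mild at 0.1 to 0.2, absent at 0, and reversed at negative values (size 0.081 to 0.087 at −0.3).

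The exposure is confined to two-time-point, within-arm comparisons of ordinal or continuous measures, and there mainly to small or moderate shifts. The power figures also assume normal data and a complete pair from every enrolled patient. Fewer pairs would lower power for a given shift under both tests, but would leave the large-sample size figures unchanged.

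**What to change.** Replace the sentence on paired data with: *Paired ordinal or continuous data will be analysed with the Wilcoxon signed-rank test (two time points) or the Friedman test (three or more time points).* Keep the Mann–Whitney test for unpaired comparisons only.

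The cost is one sentence in Statistical methods. No extra patients or data are needed, and the signed-rank test is a standard procedure in the software already named.

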### Outcome measurements

#### Primary outcome

The treatment response will be radiologically assessed every 2 months with computed tomography or magnetic resonance imaging. Objective responses will be classified according to RECIST and optimal treatment responses will be recorded. The primary endpoint is PFS, which is defined as the time from initiation of study treatment to first radiological progression or tumor-related death, whichever comes first.

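### The analysis rule stated for efficacy (ANCOVA on change from baseline) cannot be run on PFS, OS or time to progression, no listed test handles censoring, and the sample size assumes an event-based comparison

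*Protocol article*

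**What the plan says.** All references are to the protocol article.

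- **Primary outcome** defines PFS as the "time from initiation of study treatment to first radiological progression or tumor-related death, whichever comes first". **Secondary outcome** adds OS, disease control rate, time to progression and duration of treatment.
- **Sample size estimation** works from median PFS in each arm and an overall event probability of 0.77, and states that "the study would have 90% power to detect assumed median PFS of 7.0 months" in the combination arm.
- **Statistical methods** gives one rule whose scope opens with the words "For efficacy analyses and part of the safety analyses (including laboratory data and vital signs data". Under that rule, "analysis of covariance will be applied when comparing one treatment mean with another, with their respective baseline as covariates". It adds: "End points are defined as the net change of post-treatment data from baseline data".
- The other methods in that section are rank tests, Fisher, chi-square, McNemar, comparison of means, analysis of variance, linear regression and a centre-stratified Cochran-Mantel-Haenszel test. Kaplan-Meier, log-rank and Cox appear nowhere in the article.
- Three further statements do not fit. Baseline is tied to an operation: "Baseline data are defined as the data obtained before the first administration of treatment before surgery". A test for independent samples is given to pairs: "The Wilcoxon rank-sum test or the Friedman test will be used to analyze paired data". Rank tests are given to categories: "Results will be compared using the Mann–Whitney *U* test or the Kruskal–Wallis test for categorical unpaired data".

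**The concern.** The section does more than leave the PFS method open. It names a method for efficacy, and that method needs a measurement before treatment, a measurement after treatment and a mean of the difference. PFS, OS and time to progression supply none of these, and some patients will not have had the event when the data are cut.

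An analyst who follows the section must either depart from it or improvise. The nearest improvisation within the listed tests is to compare observed times by means or ranks, which counts a censored patient as having progressed on the last day seen. Censoring is heavier in the arm with longer PFS, so this shrinks the estimated benefit and wastes power. A choice made after the results are visible would also be open to challenge, because the trial is open-label.

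**Working it through.** **Inputs from the article.** Medians 3.2 and 7.0 months, two-sided α 0.025, power 90%, 2:1 allocation, event probability 0.77, 121 patients before and 153 after a 20% drop rate (Sample size estimation). Recruitment 24 months (Study participants). First patient 1 April 2019, recruitment complete about 31 March 2021, end in October 2021, so about 7 months of follow-up after accrual (Trial status). Participant timeline instead gives two years for everything, which leaves no follow-up after a 24-month recruitment.

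**Step 1. Can the efficacy rule be applied to the endpoints?**
- PFS, OS and time to progression: no baseline value, no change score, subject to censoring. The rule cannot be run.
- Duration of treatment: no baseline value; censored only for patients still on treatment at the cut-off.
- Disease control rate: a proportion, covered by the Fisher or Cochran-Mantel-Haenszel test, not by ANCOVA.

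So the rule fits none of the efficacy endpoints that the article lists. It does fit the laboratory and vital-sign data named in the same sentence.

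**Step 2. Reproduce the sample size.** Under exponential PFS, HR = 3.2/7.0 = 0.457 and (ln HR)² = 0.613. Schoenfeld's formula gives

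events = (2.241 + 1.282)² / (2/3 × 1/3 × 0.613) = 12.41 / 0.1362 = 91.2, so 92.

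92/0.77 = 119.5, so 120, against 121 stated. 121/0.8 = 151.25, so 152, or 153 to divide 2:1. The design is an event-based survival comparison. With a log-rank test, 121 × 0.77 = 93 events give 90.7% power at two-sided 0.025, so the planned size stands once such a test is named.

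**Step 3. What a substitute would cost.** The ANCOVA is undefined for PFS and cannot be simulated. The substitute assumed here is a mean test (t test) or Mann-Whitney test on observed times with censoring ignored. Other assumptions are exponential PFS, 81 against 40 patients, uniform entry over 24 months, two-sided 0.025 and 3,000 simulated trials per row. The true difference in mean PFS is (7.0 − 3.2)/ln 2 = 5.48 months.

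| Scenario | Events | Log-rank | Mean test | Mann-Whitney | Difference in mean observed times |
|---|---|---|---|---|---|
| 7 months after accrual | 86% | 93.8% | 89.9% | 86.2% | 3.74 months |
| Same, plus dropout 0.02 per month in both arms | 77% | 92.1% | 80.9% | 76.7% | 3.13 months |
| No follow-up after accrual | 68% | 88.8% | 69.8% | 64.8% | 2.51 months |

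The dropout rate in the second row was chosen to match the plan's event probability of 0.77.

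- Loss against log-rank: 3.9 and 7.6 points; 11.2 and 15.4 points; 19.0 and 24.0 points. Repeat simulations put the last pair at about 18 to 25.
- Understatement of the mean difference: 1 − 3.74/5.48 = 32%; 1 − 3.13/5.48 = 43%; 1 − 2.51/5.48 = 54%.

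**Step 4. The same at 0.05**, the level stated in Statistical methods (its mismatch with the design α of 0.025 is a separate matter). Log-rank, mean test and Mann-Whitney give 96.6%, 94.6% and 91.5% in the first row; 95.5%, 88.7% and 85.1% in the second; 93.4%, 80.5% and 74.8% in the third.

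**The case against.** **The rule may not reach PFS.** Statistical methods never names PFS, and its ANCOVA clause concerns means with a baseline. PFS has neither, and the sample size points to a survival comparison. On that reading the PFS method is merely unstated and may sit in an analysis plan that is not shown. This does not hold. The clause covers efficacy analyses without exception, the definition of end points is general, and none of the listed efficacy endpoints fits it. An analysis plan naming a log-rank test would contradict this text, and one following the text would be wrong.

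**The size rests on a substitute.** This stands. No section assigns a t test or Mann-Whitney test to PFS, or says that censored times count as events.

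**Stronger readings that the article does not support.**
- A reader might infer that the trial will produce a biased PFS result and miss its planned power. With the Trial status dates, the mean test keeps about 90% power at 0.025, and at 0.05 both substitutes exceed 90%. Large losses need heavier censoring.
- A reader might infer a false-positive problem. With equal dropout in both arms and no treatment effect, the substitutes reject in 2.0% to 2.6% of trials at nominal 2.5%. Rates of 16% to 25% arise only with unequal dropout (0.10 against 0.02 per month was tried, in either direction). The article gives no dropout figure by arm.
- A reader might infer that the test must be stratified by RAS status. Assignment of interventions names no stratification factor, and Table 1 has no separate line for RAS status, so that would be a preference.

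**Conclusion.** The point holds as a stated wrong method. The efficacy rule cannot be executed on PFS, OS or time to progression, no listed test accounts for censoring, and the section does not match an event-based design that expects about 23% censoring. This part needs no assumption.

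The numerical consequence is conditional. If mean or rank tests were used on observed times with censoring ignored, the difference in mean PFS would be understated by roughly a third to a half. Power at two-sided 0.025 would fall below log-rank by about 4 to 8 points at 86% events and about 18 to 25 points at 68% events, with 11 to 15 points at the plan's own 77%. These figures assume exponential PFS, uniform accrual and the same dropout rate in both arms.

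The misassigned rank tests and the reference to surgery, which is not part of the trial treatment, are minor. They have no shown effect on the primary result, but they suggest that the paragraph was not written for this trial.

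**What to change.** In Statistical methods, replace the efficacy sentence so that it says:

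- PFS, OS and time to progression are estimated by Kaplan-Meier and compared by a two-sided log-rank test. The test is either unstratified or stratified by a factor fixed in advance, such as centre, which the section already intends to account for.
- The hazard ratio and its confidence interval come from a Cox model with the same factors as the test.
- ANCOVA, and the definition of end points as change from baseline, apply only to laboratory and vital-sign data.

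Minor corrections in the same paragraph: use the Wilcoxon signed-rank test for paired data; do not assign Mann-Whitney or Kruskal-Wallis tests to nominal categories; delete the reference to surgery from the definition of baseline.

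The cost is wording. The sample size of 121, or 153 with dropout, is unaffected. Because the trial is open-label, the change should be made and dated before any between-arm comparison of efficacy.

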#### Data monitoring

All aspect of the study will be conducted under International Conference on Harmonization guidelines, Good Clinical Practice (GCP) guidelines, and government regulations. Monitoring (by telephone, fax, or on site) will be done by a representative of the study monitor designated by the investigators. The monitor will check CRFs for completeness, and clarify and crosscheck them with source documents. A Data Safety Monitoring Committee (DSMC) organized by the Institutional Review Board of Kaohsiung Medical University Hospital, Kaohsiung Medical University, Kaohsiung, Taiwan, will also monitor patient safety and treatment efficacy data while the study is ongoing. The DSMC is composed of two oncologists, a physician, and a statistician, none of whom is involved in the study.

The DSMC receives reports every 6 months to ensure that the investigation is conducted according to protocol design and regulatory requirements. The DSMC also monitors AEs/SAEs, and is involved in the issue of the risk–benefit to consider termination of the study.

#### Interim analysis

Early safety analysis will be performed 6 months after study is initiated.

#### Adverse events

Details of all AEs, including local and systemic reactions, will be collected including the event description, time of onset, clinicians’ assessment of severity, relation to study drugs and time of resolution or stabilization of the event. All AEs will be followed up until adequate resolution is seen. Pre-existing conditions will be recorded as medical histories. If the pre-existing condition does not change, it will not be recorded as an AE. However, if it deteriorates at any time during the study it will be recorded as an AE.

#### Auditing

Domestic authorities and the Institutional Review Board may request access to all source documents, CRFs, and other study documentation for on-site audit or inspection. The purpose of the audits is to evaluate study conduct and compliance with the protocol, standard operating procedures, GCP, and the applicable regulatory requirements. The observations and findings will be documented.

#### Consent

The free, informed and written consent of all participants will be collected by the investigator or a doctor representing them prior to final inclusion in the study. A copy of the information and consent form signed by both parties will be given to the patient; the investigator will keep the original.

#### Confidentiality

Only the patient number will be recorded in the CRF. The investigators maintain a personal patient identification list (patient numbers with corresponding patient names) to enable records to be identified.

#### Publication plan

The results of the trial will be published in international oncological, medical and scientific journals and presented at national and international congresses. The investigators will follow the rules and guidelines of the International Committee for Medical Journal Editors for authorship.

## Discussion

RTKs, such as VEGF receptor, EGFR, fibroblast growth factor receptor, platelet-derived growth factor receptor, RET and KIT, are responsible for several biological signaling pathways involved in the regulation of angiogenesis, oncogenesis and the tumor microenvironment [1]. Regorafenib is a small molecule that binds to and inhibits RTKs and therefore has antineoplastic activities. It is for this reason that regorafenib also shows various AEs, including HFSR, hypertension, thrombocytopenia, proteinuria, diarrhea, mucositis, hepatoxicity and so on. The most frequent grade 3 or higher AE related to regorafenib is HFSR, which results in dose reduction or interruption of treatment [2] and may limit the oncological efficacy of regorafenib. The occurrence of HFSR is even higher in the Asian population [11]. Modification of the dosing schedule (a change from a 160-mg dose given once daily, 21 days on, 7 days off, to 120 mg daily, 28 days on with the same accumulated dose of 3360 mg in a cycle) still has high rates of grade 3 HFSR although this recovers sooner than with the standard dosing schedule [9]. A Japanese study in which a dose reduction from 160 mg to 120 mg for 3 weeks in a 4-week cycle largely decreased the occurrence of grade 3 HFSR (75.0% in the 160-mg group and 16.7% in the 120-mg group) with comparable DCR (60.0% in the 160-mg group and 58.3% in the 120-mg group) [4]. As a result, the dose of regorafenib administered in the present study will be 120 mg once daily for the first 3 weeks in each 4-week cycle.

*UGT1A1* activity is the main factor determining cytotoxicity and AEs of irinotecan, and the US Food and Drug Administration has approved *UGT1A1* genotyping to predict irinotecan-induced severe diarrhea and neutropenia [12]. According to the *UGT1A1* genotype, an optimal dose of irinotecan can be achieved with balanced efficacy and toxicity for individuals. Lu et al. demonstrated a prognostic advantage of irinotecan dose escalation in an observational study on the basis of *UGT1A1* genotyping for mCRC treated with FOLFIRI plus bevacizumab [8], and an ongoing prospective, randomized controlled clinical trial is being conducted to examine the efficacy and safety of the aforementioned treatment [10].

In our preliminary, retrospective and observational study, in which 41 patients with mCRC were treated with regorafenib plus irinotecan dose-escalated FOLFIRI as a third- or fourth-line setting, median PFS was 6.0 months, median OS was 12.0 months and DCR was 58.5% [13]. Compared to the CORRECT and CONCUR studies, the oncological outcomes were satisfactory and treatment-related AEs were acceptable. To the best of our knowledge, there is no prospective study concerning the reintroduction of irinotecan for patients with mCRC; reintroduction of dose-escalated irinotecan for those previously treated with no irinotecan escalation may show similar results.

This is a multicenter, randomized clinical trial. There are no randomized clinical trials concerning the combination of regorafenib and irinotecan dose-escalated FOLFIRI for mCRC launched so far. Although there are aforementioned strengths to this study, this study is based on the results of a previous small, retrospective analysis and the rates of AEs of such a combination lead to some weaknesses.

This trial combines regorafenib, a targeted agent, with irinotecan dose-escalated FOLFIRI that may provide an alternative salvage treatment for previously treated mCRC.

